## Background

Cerebellar disease results in well-known motor performance deficits, including ataxia of stance and gait, limb incoordination, dysarthria, and oculomotor abnormalities. During the last decades, there has been growing evidence that cerebellar disease is not only accompanied by motor disturbances but also by cognitive and affective symptoms (see [1–3] for reviews). As early as 1998, Schmahmann and Sherman introduced the *Cerebellar Cognitive Affective/ Schmahmann Syndrome (CCAS)* [4]*.* The core symptoms of CCAS are difficulties with executive, linguistic and visuospatial functions as well as problems with the regulation of emotion and affect. Since its original description, evidence for the presence of CCAS has been accumulating in pediatric and adult patients suffering from different cerebellar diseases including various hereditary ataxias, cerebellar tumors, and cerebellar stroke [1–3]. In recent years, advances in structural and functional brain imaging allowed for detailed mapping of cognitive functions in the posterolateral cerebellar hemisphere [5–9]. As yet, diagnosis of CCAS relies on non-standardized bedside cognitive examination and, if available, detailed neuropsychological test batteries. Until recently, there has not been a validated bedside test that was able to reliably screen for CCAS in cerebellar patients – unlike well-established bedside tests for dementias or mild cognitive impairment (MCI), i.e. Mini Mental State Examination (MMSE) or Montreal Cognitive Assessment (MoCA). However, MMSE and MoCA are of limited use to screen for CCAS because cerebellar patients frequently perform within the normal range [10]. Recently, Schmahmann and colleagues [10] have developed a bedside test designed to screen for CCAS in adults. In order to develop this CCAS Scale, they first applied a broad battery of 36 well-established neuropsychological tests in a large group of cerebellar patients primarily suffering from cerebellar degeneration. In the novel CCAS Scale, tests were implemented which captured the core cognitive domains of CCAS, distinguished best between cerebellar patients and controls, and at the same time were short and easy enough to be applied in a bedside setting. These include test items for semantic and phonemic fluency, category switching, verbal registration and delayed verbal recall, digit span forward and backward, cube draw and copy, similarities, go/ no-go, and affect. Single tests can either be passed reaching a specific cut-off score or failed. CCAS is considered possible if one test is failed, probable if two tests are failed, and definite if three or more tests are failed. Version A of the CCAS Scale has then been validated in another US-American cohort of 39 adult cerebellar patients, including patients with cerebellar degeneration and focal cerebellar lesions and 55 matched healthy controls. It exhibited high values for selectivity [that is the ability to distinguish between patients and controls, or in other words preventing controls from being diagnosed as patients; possible/ probable/ definite CCAS: 78/ 93/ 100%] and reasonable sensitivity [that is the probability that a patient is identified as a patient; possible/ probable/ definite CCAS: 95/ 82/ 46%]. Furthermore, it showed modest internal consistency using Cronbach’s alpha value (= 0.59) indicating that no test item within the scale measures the exact same domain(s) as another item. Thus, no test item is redundant. Comparing patients with pure cerebellar lesions and patients with additional extracerebellar involvement the authors found that difficulties in verbal registration and delayed verbal recall were more prominent in the latter. Therefore, poor performance in these two test items is indicative of extracerebellar involvement (“red flag”). In addition to the pass/ fail criteria which are used to screen for CCAS, a total sum score is calculated which allows for follow-up examinations in individual patients [10]. Three parallel versions B-D were developed to enable repeated assessments. In the present study preliminary German versions of the CCAS Scale are introduced, and the study protocol for their validation is presented.

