##### Assessment of the CCAS Scale

The CCAS Scale will be administered in each participant at least once. In the validation process of version A, at least 40 patients and 40 controls will receive a follow-up examination with the same version of the scale to determine test-retest and interrater reliability (≥ 20 patients and ≥ 20 controls, respectively). Retesting will be done with the same version because equivalence of versions A-D has not yet been shown (see [10] and Supplements). Follow-up will take place within an interval of 14 to 56 days. A time interval is favored instead of a fixed time span between test and retest (e.g. exactly 14 days) to control for learning effects by correlating retest results with different retest time intervals.

To assess construct validity of the German version of the CCAS Scale a detailed neuropsychological testing will be done in a subset of patients (*n* ≥ 20) and controls (*n* ≥ 20) using well-established neuropsychological test batteries available in German. These will comprise the logical memory test (part I and II) of the Wechsler Memory Scale – 4th edition (WMS-IV) [18], the copy immediate and delayed recall of the Rey–Osterrieth Complex Figure Test (ROCFT) [19], and the letter-number sequencing task of the WAIS-IV [20]. These tests measure the same cognitive domains as corresponding items of the CCAS Scale. Furthermore, the German version 3 of the MoCA [21] will be assessed for direct comparison with the CCAS Scale. Finally, the Patient Health Questionnaire (PHQ-9) [22] and the German version of the EuroQuol – 5 dimension – 3 level (EQ-5D-3L) questionnaire [23] will be administered.

Validation of parallel versions of the CCAS Scale will be done the same way as for validation of parallel German versions of the MoCA [21]. Each parallel version (B/C/D) of the CCAS Scale will be tested against version A. Testing of version B/C/D and version A will be done on the same day, with the order being randomized between participants.

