##### Data analysis

Selectivity and sensitivity will be assessed using the same cut-off values for individual test items, and the same three pass/ fail criteria determined in the original study by Hoche et al. [10] (that is: possible CCAS = one test failed; probable CCAS = two tests failed; definite CCAS = three or more tests failed). To assess selectivity the percentage of true negatives will be calculated, that is the percentage of controls which have been correctly identified as controls [number of controls identified as controls/ true number of controls in the sample * 100]. To assess sensitivity the percentage of true positives will be calculated, that is the percentage of patients which have been correctly identified as patients [number of patients identified as patients/ true number of patients in the sample * 100]. In case selectivity and sensitivity falls below the values of the original CCAS Scale, selectivity and sensitivity of individual tests will be assessed. Cut-off values of single test items and/ or cut-offs defining (possible/ probable/ definite) CCAS will be adjusted to achieve high selectivity and reasonable sensitivity – comparable to the values of the original CCAS Scale.

Differences between patient groups (pure cerebellar disease vs. patients with additional extracerebellar involvement) will also be analyzed. We want to verify that difficulties in verbal registration and delayed verbal recall are indicative of extracerebellar involvement (“red flags”). In further accordance with Hoche et al. [10], Cronbach’s alpha will be used to assess the inter-relatedness of the individual test items, i.e. internal consistency.

To study construct validity of the CCAS Scale subtests of validated German versions of neuropsychological test batteries will be used as the external criterion. We will compare the percentage of patients diagnosed with CCAS based on a detailed neuropsychological test battery with the percentage of patients identified by the CCAS Scale.

Finally, correlations between age, disease duration, severity of cerebellar motor symptoms (measured by clinical ataxia scores), and total CCAS sum score will be calculated. All raw data (thus total number of failed tests respective total sum score and sub scores on single test items) will be tested for normal distribution using Kolmogorov-Smirnov tests. Parametric or non-parametric tests will be applied depending on distribution and final sample size.

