We are interested whether the scale is able to screen for CCAS in patients with degenerative diseases, but also suffering from cerebellar stroke or surgical lesions due to cerebellar tumors. In the validation study of the original American English CCAS Scale only few patients with focal cerebellar lesions were tested [10]. In part of the patients with focal lesions brain MRI scans will be available. This will allow to map dysfunction in the different cognitive domains to lesions in specific cerebellar regions. For example, we expect that language dysfunction is associated with lesions of the right posterolateral cerebellar hemisphere, and visuospatial disabilities with lesions of the left posterolateral cerebellar hemisphere [6].

A limitation of the CCAS Scale is that detection of the neuropsychiatric abnormalities highly depends on the examiner’s expertise. The authors of the US-American original were aware of this weakness and gave this item (“Affect”) a weak denominator for the total sum score [10]. Additionally, administration of more detailed scales of neuropsychiatric dysfunction are recommended [24]. In future studies, expert neuropsychiatric assessments would be of interest as a further external criterion. Furthermore, testing of construct validity has some limitations. We will perform detailed neuropsychological testing only in a subset of patients. More importantly, although the core symptoms of CCAS are well described, as yet there are no standard criteria to diagnose CCAS based on detailed neuropsychological testing. Another approach to test construct validity would be to compare CCAS scores in patients with cerebellar diseases and patients with non-cerebellar neurological diseases in the future. Despite these limitations the CCAS Scale has been shown to be more sensitive to detect cognitive and affective changes in cerebellar disease than the Mini-Mental State Examination and the Montreal Cognitive Assessment [10]. The validated German CCAS Scale will allow trained healthcare personnel to screen for cognitive and affective symptoms in patients with cerebellar diseases in German-speaking countries.

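### Construct validity is to be judged by comparing two percentages, which does not show whether the scale and the test battery flag the same patients

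*Protocol article*

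**What the plan says.** The protocol article, under Data analysis, gives the battery a clear role: "subtests of validated German versions of neuropsychological test batteries will be used as the external criterion". The next sentence states the analysis: "compare the percentage of patients diagnosed with CCAS based on a detailed neuropsychological test battery with the percentage of patients identified by the CCAS". The correlations listed later in that section relate age, disease duration and ataxia severity to the CCAS sum score. Battery scores are not among them.

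Under Assessment of the CCAS Scale, the battery consists of logical memory, the complex figure test and letter-number sequencing, given to at least 20 patients and at least 20 controls. The article says of them: "These tests measure the same cognitive domains as corresponding items of the CCAS Scale". The same section says: "The CCAS Scale will be administered in each participant at least once". Everyone in the subset will therefore have both results. A comparison with the MoCA is also announced there, without a method.

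The Perspective section lists two limits of the construct-validity work. Only a subset is tested, and "as yet there are no standard criteria to diagnose CCAS based on detailed neuropsychological testing". It does not mention agreement at patient level.

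**The concern.** An external criterion is useful if it shows whether the scale classifies the right individuals. Two overall percentages answer another question, namely whether the two methods flag a similar number of people. They can match while the people flagged differ.

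This is a named analysis that does not fit its stated purpose, so it is more than a detail the article left to a fuller plan. If the two percentages come out close, readers are likely to take that as support for construct validity, although the figures would be equally compatible with a scale unrelated to the battery.

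**Working it through.** The article gives no sample-size, power or agreement figure for construct validity, so there is no figure of the plan's own to reproduce. The check asks what equal percentages allow.

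**Inputs.** n = 20 patients, the stated minimum (Assessment of the CCAS Scale). The share flagged by the scale is taken from the original study's sensitivities, 95/82/46% for possible/probable/definite CCAS (Background). All three are shown because the article does not say which category counts as identified in this comparison. That the battery flags the same share is an assumption, chosen to represent the result that would look best.

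**Formulas.** Let each method flag a of n patients, and let x be the number flagged by both.
- Possible overlap: max(0, 2a - n) ≤ x ≤ a
- Raw agreement: po = (n - 2a + 2x)/n
- Chance agreement: pe = (a² + (n - a)²)/n²
- kappa = (po - pe)/(1 - pe)

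**Results at n = 20 with identical percentages**

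| Patient rate | a | x | Raw agreement | pe | kappa |
|---|---|---|---|---|---|
| 46% (definite) | 9 | 0 to 9 | 10% to 100% | 0.505 | -0.82 to 1.00 |
| 82% (probable) | 16 | 12 to 16 | 60% to 100% | 0.680 | -0.25 to 1.00 |
| 95% (possible) | 19 | 18 to 19 | 90% to 100% | 0.905 | -0.05 to 1.00 |

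Example for 82%: the smallest overlap is 2×16 - 20 = 12, so po = (20 - 32 + 24)/20 = 0.60, pe = (256 + 16)/400 = 0.68, and kappa = (0.60 - 0.68)/0.32 = -0.25.

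In every row the difference in percentages is zero, while kappa runs from below chance to perfect.

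**McNemar does not help.** With equal percentages the two discordant cells are equal, a - x each, so the test shows no difference at any overlap. It tests the same equality of percentages.

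**Pooling patients and controls would mislead.** Suppose 20 per group, both methods flagging 82% of patients and 7% of controls (100 minus the original selectivity of 93% for probable CCAS), and no association within either group.
- Both positive: (0.82² + 0.07²)/2 = 0.339
- Both negative: (0.18² + 0.93²)/2 = 0.449
- po = 0.787
- Overall share flagged: (0.82 + 0.07)/2 = 0.445
- pe = 0.445² + 0.555² = 0.506
- Pooled kappa = (0.787 - 0.506)/(1 - 0.506) ≈ 0.57, although kappa within each group is 0.

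**Precision of kappa.** Simulation with 40,000 draws and an assumed true kappa of 0.6 gives the central 95% of estimates:
- n = 20: about 0.20 to 0.90 with 50% positive, and about -0.07 to 1.00 with 82% positive.
- n = 65, the planned minimum of patients for version A: about 0.39 to 0.78 and 0.30 to 0.83.

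**The case against.** The strongest reply is that the flaw is limited in reach and partly disclosed. Much of that stands.

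- **Place in the study.** The Abstract presents construct validity as an addition in a subset, and the Perspective section puts high selectivity first. Selectivity, sensitivity, internal consistency and reliability do not depend on this comparison.
- **No success rule.** The article sets no threshold for construct validity, so nothing is formally accepted or rejected on the percentages.
- **Disclosure.** The lack of standard battery criteria is openly stated. A missing standard does not prevent the study from fixing its own rule, and a condensed article may leave that rule to the full plan.
- **Not declared exclusive.** The article does not say that the percentage comparison is the only analysis. The tested controls may be used elsewhere.

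A reader might also infer that the battery is too narrow, or that its memory tests mainly reflect the two verbal memory items of which the Background says "poor performance in these two test items is indicative of extracerebellar involvement". The documents do not support this as an error. The article claims only that the tests share domains with corresponding items, and it never maps individual tests to items.

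None of this repairs the comparison that is named. The disclosed limits do not include the missing patient-level agreement, and the MoCA comparison has no stated method that would supply it.

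**Conclusion.** The point holds in limited form. The stated comparison cannot show that scale and battery flag the same patients. At n = 20, and with equal percentages at the original scale's patient rates, raw agreement may be as low as 10, 60 or 90% and kappa as low as -0.82, -0.25 or -0.05. These bounds assume equal shares flagged by both methods and the minimum subset size.

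Two stronger conclusions should not be drawn. First, a reader might infer that the scale could disagree with the battery in every patient and still pass. With equal percentages, that requires each method to flag exactly 10 of 20 with no overlap, and it cannot happen at any of the three original rates. Second, the percentages are not wholly uninformative. Unequal percentages prove some disagreement, and very high rates force high raw overlap. What stays undetermined is agreement beyond chance.

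The point should be corrected before analysis. It does not put the study's main results at risk.

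**What to change.** Replace the percentage comparison as the main construct-validity analysis.

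1. Within the patient group, cross-classify each patient's battery result against the scale result in a 2x2 table. Fix the battery rule, and the CCAS category or categories used, before the data are examined.
2. Report positive agreement, negative agreement and kappa, each with a confidence interval. The two percentages can remain as description.
3. Add correlations between CCAS items and the battery tests of the same domain, calculated within group or adjusted for group. The tested controls then contribute without inflating the association.
4. Do not pool patients and controls for kappa, and do not present McNemar as evidence of agreement.
5. Limit the construct-validity claim to the domains the battery covers.

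The cost is a change of wording and a modest amount of analysis, because the paired data are already planned. The drawback is a narrower claim and visibly imprecise estimates at about 20 patients, which the report should acknowledge.

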**Methods:**

A preliminary German version has been created from the original CCAS Scale using a standardized translation procedure. This version has been pre-tested in cerebellar patients and healthy controls including medical experts and laypersons to ensure that instructions are well understandable, and that no information has been lost or added during translation. This preliminary German version will be validated in a minimum of 65 patients with cerebellar disease and 65 matched healthy controls. We test whether selectivity and sensitivity of the German CCAS Scale is comparable to the original CCAS Scale using the same cut-off values for each of the test items, and the same pass/ fail criteria to determine the presence of CCAS. Furthermore, internal consistency, test-retest and interrater reliability will be evaluated. In addition, construct validity will be tested in a subset of patients and controls in whom detailed neuropsychological testing will be available. Secondary aims will be examination of possible correlations between clinical features (e.g. disease duration, clinical ataxia scores) and CCAS scores.

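### The only stated construct-validity comparison sets two overall percentages of patients side by side, which does not show that the CCAS Scale and the battery identify the same patients

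*Protocol article*

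**What the plan says.** The Abstract (Methods) announces that "construct validity will be tested in a subset of patients and controls in whom detailed neuropsychological testing will be available". Under Assessment of the CCAS Scale, every participant takes the scale at least once, and "a detailed neuropsychological testing will be done in a subset of patients" and of controls, at least 20 each. The tests listed there are logical memory, the complex figure test and letter-number sequencing. The section adds: "These tests measure the same cognitive domains as corresponding items of the CCAS Scale".

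Under Data analysis, "subtests of validated German versions of neuropsychological test batteries will be used as the external criterion". The comparison that follows is to "compare the percentage of patients diagnosed with CCAS based on a detailed neuropsychological test battery with the percentage of patients identified by the CCAS Scale". No other analysis of scale against battery is stated. The correlations planned in the same section are of a different kind: "correlations between age, disease duration, severity of cerebellar motor symptoms (measured by clinical ataxia scores), and total CCAS sum score will be calculated". The Montreal Cognitive Assessment is also to be compared directly with the scale, but it is listed apart from the battery tests and no method is given.

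The Perspective section concedes two limits on construct validity: only a subset is tested, and no standard criteria exist for diagnosing CCAS from detailed testing.

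**The concern.** An external criterion is meant to show whether the scale flags the people whom the criterion flags. Each subset member has a result on both instruments, so the data form a paired two-by-two table. The stated comparison uses only the margins of that table. Equal margins mean that both methods flag the same number of patients, not the same patients.

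The comparison can mislead in the other direction too. Two methods that rank patients in the same order but cut at different points give different percentages and would look discordant.

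The comparison is also worded for patients only. Controls are put through the battery for construct validity, yet the section that describes the analysis states no role for them.

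Construct validity is one component of the validation, which Study aims lists as the second primary aim. As worded, similar percentages could be reported as support for that component when scale and battery agree no better than chance.

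**Working it through.** The article gives no sample-size, power or agreement figure for construct validity, so there is nothing to reproduce. The check asks what equal percentages imply about agreement.

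**Inputs.** Subset size n = 20 patients, the stated minimum (Assessment of the CCAS Scale). Share of patients positive, p: the original scale's sensitivities, "possible/ probable/ definite CCAS: 95/ 82/ 46" percent (Background). That these rates hold in the German subset, and for the battery as well as the scale, is an assumption made for illustration.

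**1. Range of agreement when both percentages equal p.**
- Highest agreement: 1, when the same patients are flagged.
- Lowest agreement: |2p − 1|, when the flagged groups overlap as little as possible.
- Agreement expected by chance: p² + (1 − p)². This is also the agreement of two independent methods.
- Kappa = (observed − chance) / (1 − chance).

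| p | lowest agreement | chance agreement | lowest kappa | highest kappa |
|---|---|---|---|---|
| 0.95 | 0.90 | 0.9025 + 0.0025 = 0.905 | (0.90 − 0.905)/0.095 = −0.05 | 1 |
| 0.82 | 0.64 | 0.6724 + 0.0324 = 0.705 | (0.64 − 0.7048)/0.2952 = −0.22 | 1 |
| 0.46 | 0.08 | 0.2116 + 0.2916 = 0.503 | (0.08 − 0.5032)/0.4968 = −0.85 | 1 |

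**2. The same in whole patients.** Let 9 of 20 be positive on each method (45% against 45%). One table that fits has 0 positive on both, 9 on the scale only, 9 on the battery only and 2 on neither. Agreement is 2/20 = 10%, chance agreement is 0.2025 + 0.3025 = 0.505, and kappa is (0.10 − 0.505)/0.495 = −0.82. Perfect agreement (9 on both, 11 on neither, kappa 1) gives the same two percentages.

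**3. How often unrelated methods look alike.** Let the methods be independent (true kappa 0) with the same p. Write b for patients positive on the scale only and c for those positive on the battery only. The percentages differ by (b − c)/20, so a difference of 10 points or less means |b − c| ≤ 2. Each of b and c has cell probability p(1 − p): 0.0475, 0.1476 and 0.2484 at the three rates. Summing the exact multinomial probabilities gives 0.93 at 95%, 0.70 at 82% and 0.57 at 46%.

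**4. The converse.** The scale's own levels serve as an example. Anyone who fails three or more tests has also failed two, so every definite case also meets the probable criterion. The percentages are nevertheless 46 and 82, which is 36 points apart for two cuts of one count. Kappa between these two cuts is also modest: observed agreement is 1 − 0.36 = 0.64, chance agreement is 0.82 × 0.46 + 0.18 × 0.54 = 0.474, and kappa is (0.64 − 0.474)/0.526 = 0.32. A yes/no agreement measure therefore also depends on where the thresholds lie, which favours correlating scores first.

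**5. A paired test of the percentages.** McNemar's test would not repair this. It tests whether b and c are equal in expectation, which is again equality of margins. The article names no test.

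**The case against.** The strongest reply is that this is a condensed article. Construct validity gets two sentences, and nothing in them excludes a cross-tabulation or item-level correlations in a fuller document. The remark that battery tests and scale items share domains would suit such an analysis. This stands as a caution about what the sponsor may in fact do. It does not remove the point, because the article commits to a particular comparison, and more detail on that comparison would not make it answer the question.

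A second reply is that the authors concede weaknesses. They do, but not this one: the flaw would remain if the whole cohort were tested and agreed diagnostic criteria existed. The concession does limit the remedy, since any yes/no battery diagnosis, and hence kappa, rests on a rule for which no standard exists.

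Third, the extreme values are algebraic bounds. Kappa near −0.85 is implausible for tests said to measure shared domains in the same patients. That is fair; the bounds show what equal percentages fail to exclude, not what is expected.

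A reader might infer that the control results, half of the battery data at the planned minimum, are discarded. The documents do not support that. The stated comparison concerns patients, but controls are not excluded and could, for example, supply reference performance. What can be said is that no use of them is stated.

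**Conclusion.** The point holds for the comparison as stated. Similar percentages of patients do not show that the scale and the battery identify the same patients, and different percentages do not show that the two are unrelated. The algebra holds at any rate strictly between 0% and 100%. The particular sizes (8% to 100% agreement at 46%; probabilities of 0.93, 0.70 and 0.57) rest on the US rates applying to both methods and, for the probabilities, on n = 20 and independence.

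It should be fixed, but it does not undermine the study. A reader might infer that construct validity cannot be shown here at all, or that the validation fails. Neither follows. The paired data will be collected and can answer the question once analysed per person. Selectivity, sensitivity, internal consistency and reliability do not depend on this comparison, and the Perspective section names high selectivity as the primary aim of the validation.

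**What to change.** Reword the construct-validity paragraph under Data analysis so that the main analysis is per person.

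- **First,** correlate each CCAS item that has a corresponding battery subtest with that subtest's score, in patients and controls separately, with 95% confidence intervals. Name the pairs in advance; the article refers to corresponding items without listing them. This needs no battery-based diagnosis.
- **In addition,** cross-tabulate scale result against battery result, with the battery rule and one CCAS threshold fixed beforehand. Report positive and negative agreement and kappa, with 95% confidence intervals.
- **Keep** the two percentages as description only, and state what the control results are used for.

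The cost is wording; no new data are needed. The downside is that with about 20 per group the estimates will be imprecise (for example, 16 of 20 has an exact 95% interval of 56% to 94%), and the result may look less favourable than two similar percentages.
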